# Protocol for the COG-UK hospital-onset COVID-19 infection (HOCI) multicentre interventional clinical study: evaluating the efficacy of rapid genome sequencing of SARS-CoV-2 in limiting the spread of COVID-19 in UK NHS hospitals

**DOI:** 10.1136/bmjopen-2021-052514

**Published:** 2022-04-18

**Keywords:** COVID-19, infection control, molecular biology, epidemiology

## Abstract

**Objectives:**

Nosocomial transmission of SARS-CoV-2 has been a significant cause of mortality in National Health Service (NHS) hospitals during the COVID-19 pandemic. The COG-UK Consortium Hospital-Onset COVID-19 Infections (COG-UK HOCI) study aims to evaluate whether the use of rapid whole-genome sequencing of SARS-CoV-2, supported by a novel probabilistic reporting methodology, can inform infection prevention and control (IPC) practice within NHS hospital settings.

**Design:**

Multicentre, prospective, interventional, superiority study.

**Setting:**

14 participating NHS hospitals over winter–spring 2020/2021 in the UK.

**Participants:**

Eligible patients must be admitted to hospital with first-confirmed SARS-CoV-2 PCR-positive test result >48 hour from time of admission, where COVID-19 diagnosis not suspected on admission. The projected sample size is 2380 patients.

**Intervention:**

The intervention is the return of a sequence report, within 48 hours in one phase (rapid local lab processing) and within 5–10 days in a second phase (mimicking central lab), comparing the viral genome from an eligible study participant with others within and outside the hospital site.

**Primary and secondary outcome measures:**

The primary outcomes are incidence of Public Health England (PHE)/IPC-defined SARS-CoV-2 hospital-acquired infection during the baseline and two interventional phases, and proportion of hospital-onset cases with genomic evidence of transmission linkage following implementation of the intervention where such linkage was not suspected by initial IPC investigation. Secondary outcomes include incidence of hospital outbreaks, with and without sequencing data; actual and desirable changes to IPC actions; periods of healthcare worker (HCW) absence. Health economic analysis will be conducted to determine cost benefit of the intervention. A process evaluation using qualitative interviews with HCWs will be conducted alongside the study.

**Trial registration number:**

ISRCTN50212645. Pre-results stage. This manuscript is based on protocol V.6.0. 2 September 2021.

Strengths and limitations of this studyHarnesses infrastructure of UK’s existing national COVID-19 genome sequencing platform.First prospective interventional study to assess effectiveness of genomic sequencing for infection prevention and control in an unbiased patient selection in secondary care.Awarded UK National Institute of Health Research Urgent Public Health status, ensuring prioritisation of recruitment.A limitation is that the study does not have a randomised controlled design.

## Introduction

### Background

Hospitals are recognised to be a major risk for the spread of infections despite the universal introduction of infection control measures. For SARS-CoV-2, nosocomial spread of infection presents an additional and significant health risk to patients and healthcare workers (HCW).^1^ During epidemics, infection prevention and control (IPC) practice is further complicated by the difficulties of distinguishing community and hospital-acquired infections. This can lead to erroneous identification of nosocomial transmission, leading to unnecessary IPC efforts. True nosocomial transmission events may be missed with appropriate interventions not performed, thereby putting patients and HCW at increased risk. The epidemiological determination of infection timing for SARS-CoV-2 is made especially challenging by its prolonged incubation period in distinguishing community from nosocomial transmission.

There is now good evidence that genome sequencing of epidemic viruses, together with standard IPC, better defines nosocomial transmissions and, depending on the virus, better identifies routes of transmission, than IPC alone.^2–4^ The development of rapid sequencing methods enables sequencing of potentially linked or unlinked SARS-CoV-2 genomes within 48 hours. This timescale is short enough to inform clinically relevant IPC decisions in near-real time. Although some studies have described the prospective use of viral sequencing to inform infection control for SARS-CoV-2, none has prospectively evaluated the impact of sequencing on the incidence of nosocomial infection or on infection control actions across all cases with hospital onset.^5–7^

While SARS-CoV-2 has a low mutation rate (estimated at around 2.5 changes per genome per month), sufficient viral diversity exists to identify cases where patient and HCW infections that are clustered in time and space are in fact due to different SARS-CoV-2 genotypes.^8^ Such information could rapidly exclude nosocomial transmission as the cause of the cluster and redirect IPC intervention to where needed most.

Confirmation of SARS-CoV-2 transmission to patients and HCWs may be more challenging with a single-observed mutation between two genomes, feasibly representing anything between 1 and 10 transmissions. Identical genomes will not necessarily evidence a close-link between two cases. Nonetheless, by comparing genotypes detected within the hospital setting and the surrounding community, it may be possible to reveal unsuspected nosocomial transmission where comparatively uncommon genotypes are apparently linked or cluster in time and space.

The Consortium Hospital-Onset COVID-19 Infections-UK (COG-UK) initiative aims to sequence as many SARS-CoV-2 viruses as possible across the UK for public health planning. It also provides an important and unique opportunity to test whether viral sequence data produced in near-real-time could also reduce uncertainties around nosocomial transmission events, better direct IPC effort, improve hospital functioning and reduce the role of hospitals as a source of infection to the community.^9^

COG-UK HOCI* will harness the COG-UK sequencing platform, with its mixed model of smaller sequencing hubs located close to hospitals and a large centralised hub sequencing most viruses. It will identify not only whether rapid viral sequencing is useful for patient management, but how time-critical this might be; turnaround times for sequence data from a central hub are likely to be longer (5–10 days) than those from local sequencing hubs (<48 hours).

*Note that while HOCI was the preferred term at the study’s inception, evolution of the terminology now favours references be made to ‘hospital-onset SARS-CoV-2 infections’

### Objective

The study will evaluate the contribution of whole-genome sequencing combined with a novel viral sequence report design to IPC investigation and response to cases of hospital-onset COVID-19infection, and whether this can reduce the overall incidence of hospital-acquired infections.^10^

## Methods and analysis

### Study design

COG-UK HOCI is a prospective, interventional, superiority clinical study, comprising three distinct phases with a possible fourth, dependant on interim data analysis.

In the first phase, all sites will collect baseline (non-interventional) eligible patient data for a period of 4 weeks to characterise each site’s usual practice in infection control in response to hospital-onset COVID-19 cases. This phase may include standard of care use of genome sequencing (eg, limited outbreak response analysis).

In the second and third phases, the study intervention will be applied on top of standard of care infection control practices.

The second phase requires ‘rapid’ turnaround of genome sequencing and sequence linkage report generation (ie, within 48 hours of first diagnostic SARS-CoV-2 PCR-positive result). This phase will be applied to all hospital onset COVID-19 cases meeting the eligibility criteria over an 8-week period.

The third phase is similar to the second, except that a 5–10 day turnaround time of genome sequencing and sequence report generation should be applied to mimic the use of a central sequencing laboratory. This phase will apply to all sites and last for 4 weeks.

The second and third phases may be applied in the reverse order at some sites, both for logistical reasons (ie, fine-tuning of rapid turnaround of whole-genome sequences) and also to ensure differences between sites in the calendar dates of each phase.

On review of interim analysis data, the study’s joint oversight committee may recommend a fourth phase for all sites comprising a second baseline period; this would be applied where the initial baseline data collection period occurred at a time of very high or low COVID-19 prevalence at the sites, whereby collecting data on standard practice could be unviable.

This will be a sequential study, with each National Health Service (NHS) Trust acting as its own control.

The total study duration per site will accordingly be 16–20 weeks, though it is likely that pauses in data collection will occur over the winter holiday break period due to most sequencing labs closing or moving to skeletal operations during this time.

### Intervention

#### Overview

The study intervention is a SARS-CoV-2 genomic sequencing data report (see figure 1) delivered to the NHS site’s IPC teams, either within 24–48 hours of the sample from the patient being confirmed as positive for SARS-CoV-2 (rapid genomic sequencing locally) or within 5–10 days (local genomic sequencing to mimic use of a centralised lab).^11^

**Figure 1 F1:**
[figure not shown]
Example of HOCI Sequence Reporting Tool (SRT) Report Output. COG-UK HOCI, COG-UK Consortium Hospital-Onset COVID-19 Infections; HCW, healthcare worker; IPC, infection prevention and control.

Microbiology and IPC teams will be trained to interpret the results. An expert sequence interpretation team (a subset of the Study Team) will be available 7 days a week by phone and online to discuss results where required with IPC teams and to provide guidance on best practice.

#### Genomic sequence reporting tool

The genomic sequence report tool combines epidemiological and consensus sequence data in order to provide a rapid assessment of the probability of hospital acquired infection (HAI) among new HOCI study cases and to identify infections that could plausibly constitute a hospital outbreak event.^12^

The internal calculations use a combination of admission-to-symptom-onset intervals and differences between the observed proportion of close sequence matches (defined as a maximum pairwise difference of two-single nucleotide polymorphisms; SNPs) for viral samples obtained from various locations (ie, same ward, same hospital, within the community) to estimate the probability that the patient’s SARS-CoV-2 infection was acquired in hospital.

The report generation algorithm is designed to run quickly and reliably, without the need for local model checking, thereby reducing the need for expert bioinformatics input during operation.

#### Sequence reports

The summary report for each focus sequence submitted, corresponding to a single HOCI case, will comprise:

The lineage assignment for the focus sequence.A list of the details of any close sequence matches from samples on the same ward as the focus sequence in the previous 3 weeks, with estimated probability of infection having occurred from a source on the ward (reported as low, moderately low, probable, high, very high).A list of the details of any close sequence matches from samples obtained within the hospital but not same ward as the focus sequence in the previous 3 weeks, with estimated probability of infection having occurred from a source in the institution (reported as low, moderately low, probable, high, very high).Estimated probability of infection from a visitor to the ward (reported as low, moderately low, probable, high, very high).Estimated probability of community-acquired infection (reported as low, moderately low, probable, high, very high).A graphical summary displaying sample dates of close sequence matches at the ward and hospital levels, along with the total number of samples obtained over the previous 3 weeks.

A detailed report will also be returned to virology labs for each focus sequence, containing additional details of all the recent sequences obtained within the given ward and hospital that have contributed to the output summarised in the summary report, and their similarity with respect to the focus sequence.

#### Allocation of intervention

All sites will engage in the various study phases sequentially; there will be no allocation of intervention either by site or at patient level for this study.

### Population

#### Setting

Fourteen NHS Trusts/Heath Boards across England and Scotland will participate. Sites will be set-up either as all hospitals within a Trust or a single hospital selected from within the Trust. This decision will be site-led and based on available research team, infection control team and sequencing resource. Sites will be selected to span tertiary referral centres through to district hospitals, primarily in urban or suburban settings. Screening and routine testing of patients and HCWs will follow local health guidance.

#### Inclusion criteria

Patients will be considered eligible only where they are an inpatient with first confirmed positive test for SARS-CoV-2>48 hours after admission, where they were not suspected to have COVID-19 at time of admission.

Participants may be of any age to be included in the study.

There are no exclusion criteria.

#### Recruitment

Viral sequencing will be attempted for every confirmed case of SARS-CoV-2 in hospital patients and HCW, but it is not possible to assess clinical and infection control outcomes for every confirmed case. This study will, therefore, focus on the subset of patients with hospital-onset SARS-CoV-2, since this is where the additional knowledge potentially provided by viral sequencing is likely to have the greatest impact for IPC teams. HCWs will not be enrolled as index cases but will be part of the reference sequence data set where available. Patient samples will be collected and sequenced per standard NHS Trust practice in support of pre-existing site arrangements to provide SARS-CoV-2 sequence data to COG-UK in support of national genomic surveillance for public health.

#### Patient consent

Consent for participant (both patient and HCW) involvement will not be sought for COG-UK HOCI study. This approach relies on the Health Service (Control of Patient Information) Regulations 2002 (SI 1438), specifically Regulation 3 (Communicable disease and other risks to public health), and Regulation 7 (the processing of confidential information for medical research).

### Study outcomes

#### Primary outcomes

Incidence rate of PHE/IPC-defined SARS-CoV-2 HAIs (defined as SARS-CoV-2 cases with an interval of ≥8 days from admission to symptom onset, if known, or sample date), measured as incidence rate of recorded cases per week per 100 inpatients, during each phase of the study.Identification of linkage to individuals within an outbreak of SARS-CoV-2 nosocomial transmission using sequencing report data for HOCIs in whom this was not identified by presequencing IPC evaluation, for each enrolled patient during study phases in which the sequence reporting tool is in use.

#### Secondary outcomes

Incidence rate of IPC-defined SARS-CoV-2 hospital outbreaks, defined as cases of hospital transmission linked by location and with intervals between diagnoses no greater than 28 days, measured as incidence rate of outbreak events per week per 100 inpatients during each phase of the study.Incidence rate of IPC+sequencing-defined SARS-CoV-2 hospital outbreaks involving HOCI cases, defined as for IPC-defined SARS-CoV-2 hospital outbreaks with the additional condition of clustering of viral sequences and measured as outbreak events per week per 100 inpatients during study phases in which the sequence reporting tool is in use. Genetic clusters are defined as having maximum viral sequence pairwise SNP distance of 2 between each individual included and their nearest neighbour within the cluster.Changes to IPC actions implemented following receipt of SARS-CoV-2 sequence report, for each enrolled patient during study phases, in which the sequence reporting tool is in use.Changes to IPC actions that would ideally have been implemented but may not have been following receipt of SARS-CoV-2 sequence report, for each enrolled patient during study phases in which the sequence reporting tool is in use.Health economic benefit of both slow and rapid sequencing reports to IPC against baseline.The number of HCW periods of sickness/self-isolation, assessed as a proportion of the number of staff usually on those wards impacted by HOCI cases, for all phases of the study.

In collaboration with IPC teams at NHS sites, the outcome data above will be collected using case report forms (CRFs) specifically designed for this study. These will be prospectively completed during the course of the study and stored in a central study database.

#### Exploratory outcomes

Additionally, descriptive summaries of sequence report results will be generated, including number of close sequence matches on ward and within hospital; probability of infection source; whether HCWs are reported within close sequence matches.

For the process evaluation, the qualitative team will seek to understand how the intervention worked in practice across a representative sample of study sites (n=5). This will include how the context shaped the intervention; how key intervention components and causal mechanisms operated for IPC teams and hospital planners, and how the intervention changed the study outcomes.

### Sample size and power

The projected total sample size is 2380 patients.

There is uncertainty in the number of HOCIs that will be identified at each site during each of the intervention periods, with the rapid testing phase being 8 weeks’ duration. Based on clinical experience of first wave and discussion with the principal investigators, we assume there may be an average of 10 HOCIs/week per site during this intervention period, a total of 80 per site. Within a typical site this will allow us to estimate the proportion of HOCIs with genotypic linkage to any other case(s) not detected by IPC processes with minimum precision of±9.4%. Similarly, we can estimate the proportion of HOCIs where an action is taken that would not have occurred without sequencing within±9.4%. We shall also calculate pooled estimates of these proportions across the 14 sites, leading to estimation within±6.5% assuming an intracluster correlation coefficient of 0.05.

Comparing the proportion of HOCIs with genotypic linkage to any other case(s) not detected by IPC processes between rapid testing and slow testing phases across all sites, the study would have at least 80% power to detect a percentage point difference of 11%. This corresponds to a two-sided test with alpha=0.05, considering proportions of 55.5% vs 44.5% which would be associated with minimum power for a difference of this magnitude.

For the outcome of weekly incidence of IPC-defined HOCIs, using an approximate normal distribution for weekly counts there is 86.7% power to demonstrate a reduction from 12 IPC-defined HOCIs per week in the baseline phase to 10 per week during the rapid testing phase across all sites, under 5% significance level two-tailed testing. However, these calculations correspond to a variance of 12 for weekly counts based on the Poisson distribution, but the presence of over-dispersion of weekly counts would lead to a lower power to detect a difference. Using an overdispersion parameter of 0.82 based on retrospective analysis of data from Sheffield and Glasgow (dataset as described by Stirrup *et al*) results in 81% power to detect a reduction in mean weekly incidence from 12.5 to 10.^10^

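### Within-site precision of ±9.4% does not follow from 80 HOCIs per site; the worst-case 95% half-width is ±11.0%

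*Protocol article*

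**What the plan says.** All the relevant figures are in the Sample size and power section of the protocol article.

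- **Cases per site.** The rapid phase is described "with the rapid testing phase being 8 weeks’ duration", and the authors assume "an average of 10 HOCIs/week per site during this intervention period, a total of 80 per site".
- **Within-site precision, linkage.** A typical site is said to be able to estimate the proportion of HOCIs with genotypic linkage "not detected by IPC processes with minimum precision of±9.4" per cent.
- **Within-site precision, actions.** The same figure is given for "the proportion of HOCIs where an action is taken that would not have occurred without sequencing within±9.4" per cent.
- **Pooled precision.** The authors add: "We shall also calculate pooled estimates of these proportions across the 14 sites", "leading to estimation within±6.5% assuming an intracluster correlation coefficient of 0.05".

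No expected proportion and no confidence level are given for these precision figures. The Statistical analysis section sets a two-sided 0.05 level for tests and 95% intervals for the incidence rate ratios.

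**The concern.** Every input to the within-site figure is printed next to it, and the figure does not follow from them. The word *minimum* points to the least favourable proportion, 50%, at which 80 cases give a half-width nearer 11% than 9.4%.

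Previously unidentified linkage is the second primary outcome, and changes to infection-control actions are a secondary outcome. For both, the Statistical analysis section makes summary statistics, overall and by site, the focus of analysis. The site results are to be set informally against how fully each site implemented the intervention. The ±9.4% is the only stated support for how precisely one site can be read, so a reader planning or judging that comparison would expect tighter site estimates than the design gives.

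**Working it through.** **Inputs**

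- Cases per site: n = 10 per week × 8 weeks = 80 (Sample size and power).
- Sites: 14. Intracluster correlation: 0.05 (same section).
- Proportion: p = 0.5, the worst case, inferred from the word *minimum*.
- Confidence level: 95%, so z = 1.96. This is an assumption, taken from the two-sided 0.05 in Statistical analysis and supported by step 1.

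**Step 1. Reproduce the pooled figure.**

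- Design effect = 1 + (80 − 1) × 0.05 = 4.95.
- Total cases = 14 × 80 = 1120; effective number = 1120 / 4.95 = 226.3.
- Half-width = 1.96 × √(0.25 / 226.3) = 6.51%.

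The article prints ±6.5%. It reproduces with 80 per site, p = 0.5 and 95%. At 90% it would be 5.5%.

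**Step 2. Apply the same convention within a site.**

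Half-width = 1.96 × √(0.25 / 80) = 10.96%, that is ±11.0%. The article prints ±9.4%.

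**Step 3. Try other interval methods at n = 80, p = 0.5.**

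| Method | 95% | 90% |
|---|---|---|
| Wald | 10.96% | 9.20% |
| Wilson | 10.70% | 9.04% |
| Agresti-Coull | 10.70% | 9.04% |
| Jeffreys | 10.79% | 9.09% |
| Clopper-Pearson | 11.40% | 9.70% |

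None gives 9.4%.

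**Step 4. What would give ±9.4% (Wald)?**

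- At p = 0.5 and 95%: n = 0.25 × (1.96 / 0.094)² = 108.7, about 109 per site. The pooled half-width would then be 6.35%, not 6.5%.
- At n = 80 and 95%: p(1 − p) = 80 × (0.094 / 1.96)² = 0.184, so p is about 0.24 or 0.76. Neither is the worst case.
- At n = 80 and p = 0.5: a confidence level of 90.7%.
- Both intervention phases together, 12 weeks at 10 per week (n = 120), give 8.95%.
- The whole projected sample per site, 2380 / 14 = 170, gives 7.5%.

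**Step 5. A check that needs neither p nor the confidence level.**

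With the normal approximation and the same p and z in both figures, pooled half-width / within-site half-width = √(design effect / 14) = √(4.95 / 14) = 0.595.

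The printed ratio is 6.5 / 9.4 = 0.69. Rounding does not explain the gap: the extremes are 6.45 / 9.45 = 0.68 and 6.55 / 9.35 = 0.70. If ±9.4% were right, the pooled figure would be 9.4 × 0.595 = 5.6%. If ±6.5% is right, the within-site figure is 6.5 / 0.595 = 10.9%, which agrees with step 2 up to rounding.

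**Size.** 10.96 − 9.4 = 1.56 percentage points; 10.96 / 9.4 = 1.17, so the true half-width is 17% wider. 109 / 80 = 1.36, so the printed figure implies 36% more cases per site.

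**The case against.** The arithmetic is hard to dispute, so the best case against the point concerns its weight and its explanation.

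- **Little hangs on the figure.** No sample size, test or decision rule in the article is derived from it. The same outcome also has a pooled precision, which is correct, and a separate power statement for rapid against slow sequencing. The reported intervals will come from the observed data, so a planning figure cannot make them too narrow. This stands, and it limits the consequence to the planning text.
- **The 80 is itself soft.** The section says openly that case numbers are uncertain. At p = 0.5, 60 cases would give ±12.7% and 108 would give ±9.4%, so ordinary variation in caseload can exceed the discrepancy. This is true, but the article derives its figure from 80, and that derivation fails.
- **The basis is not stated.** The article gives no p and no confidence level, and the actions sentence does not repeat the word *minimum*. A different proportion, a different confidence level, a leftover from another calculation or a typing error could each lie behind 9.4. The cause therefore cannot be established. A different p or confidence level used for both figures would not remove the contradiction, because both cancel in step 5. The article gives no sign that the two figures use different ones.

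**Conclusion.** The within-site ±9.4% is wrong as written. For 80 HOCIs per site the worst-case 95% half-width is ±11.0%, for both linkage and infection-control actions. The printed figure is about 1.6 percentage points too small.

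This rests on two readings that the article does not spell out: p = 0.5 and 95% confidence. Both are supported by the pooled ±6.5%, which they reproduce. Even without them, ±9.4% and ±6.5% cannot both hold for 80 per site, 14 sites and an intracluster correlation of 0.05 on any common proportion and confidence level. Why 9.4 was printed is not known.

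The effect is modest and confined to the planned precision of site-level descriptive estimates. Nothing here calls the pooled precision into question or requires a change of design.

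**What to change.** In Sample size and power, replace ±9.4% with ±11.0% in both sentences, and say that this is the 95% half-width at a proportion of 50% with 80 cases. Keep the 80 per site and the pooled ±6.5%. If another number of cases, proportion or confidence level was intended for ±9.4%, state it and show how it fits with ±6.5%.

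The cost is two numbers and one clause of text. The stated site-level precision becomes slightly less favourable.
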